### Measures and data collection

The primary outcome measures in this study are health-related quality of life measured by the RAND-36 [35,36] and disability in activities of daily living (ADL, including mobility) and instrumental activities of daily living (IADL), assessed using the Groningen Activity Restriction Scale (GARS) [37]. Both instruments appear to be valid, reliable and suitable for self-completion in older people [38,39]. These outcomes, together with the secondary outcome attitude towards ageing (subscale attitude toward ageing from the PGC Morale Scale) [40] are included in a questionnaire send to older people by postal mail at baseline, 6-months, 12-months and 18-months follow-up. The baseline questionnaire also gathers data about socio-demographic variables (i.e., age, gender, ethnicity, educational level, marital status, household composition) to provide insight into characteristics of the target population. Assistance is provided to older people who are unable to self-complete the questionnaires or those with many missing items (mostly people with poor physical or mental health).

Additional secondary outcomes are admission to a nursing home or home for older people, health care utilisation, and mortality. General practices register these outcomes continuously during the study period in the GP Information System and data are extracted for each patient after 18-months follow-up. Furthermore, health care utilisation is also recorded in the [G]OLD care booklet. Older people receive this booklet at baseline and are requested to take it with them to each contact with professional health care providers for 18 months. In this booklet, patients and/or care providers indicate the reason for the contact, type of health problems or complaints, and follow-up activities. Table 2 presents all outcome measures, their operationalisation and timing of data collection.

**Table 2 T2:** **Measures**, **operationalisation and timing of data collection**

**Measures**	**Operationalisation**	**No**. **of items**	**Range score**^*^	**Timing data collection**^†^
*Primary outcomes*				
Health-related quality of life	RAND-36 [35,36]	36	N/A	T_0_, T_1_, T_2_, T_3_
Disability	GARS [37]	18	18–72	T_0_, T_1_, T_2_, T_3_
	IADL	11	11-44	
	ADL	7	7–28	
*Secondary outcomes*				
Attitude towards ageing	Subscale attitude toward own ageing - PGC Morale Scale [40]	5	0–5	T_0_, T_1_, T_2_, T_3_
Health care utilisation	Number of contacts with different health care providers (i.e., GP consultations, hospital admission)	3	N/A	T_0_
		N/A	N/A	CR_GP and CR_E
Admission to nursing home or home for older people	Number of admissions and time to admission from T_0_ to T_3_	N/A	N/A	CR_GP
Mortality	Number of deaths from T_0_ to T_3_	N/A	N/A	CR_GP

* Underlined scores indicate the most favourable scores. N/A means not applicable.

† T_0_ = postal questionnaire at the start of the study; T1 = postal questionnaire at 6-months follow-up; T2 = postal questionnaire at 12-months follow-up; T3 = postal questionnaire at 18-months follow-up; CR_GP = continuous registration during study in GP’s Information System; CR_E = continuous registration during study by older people in [G]OLD care booklet.

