### Process evaluation

A thorough process evaluation is conducted aiming to investigate to what extent the different components of the [G]OLD-protocol are implemented within general practices as planned (e.g., barriers and facilitators for implementation) and the feasibility of the protocol for both patients and caregivers. Ultimately, the results may provide information for further implementation of [G]OLD within general practices. Qualitative and quantitative process data are collected with either formative or summative purposes among GPs, practice nurses and older people according to the comprehensive and systematic approach proposed by Saunders and colleagues [41] (for details, see Table 3).

**Table 3 T3:** Data collection as part of the process evaluation

**Components**	**Operationalisation**	**Data collection Tools/****Procedures**
*Fidelity* (*quality*)	Extent to which the [G]OLD-protocol was implemented as planned	Evaluation form training PNs
		Individual interviews PNs, GPs and older people
		Feedback sessions PNs
		[G]OLD-instrument and care and treatment plan
*Dose delivered* (*completeness*)	Extent to which all aspects of [G]OLD-protocol are delivered to general practices and older people	Evaluation form training PNs
		Individual interviews PNs, GPs and older people
		Feedback sessions PNs
		[G]OLD-instrument and care and treatment plan
*Dose received* (*exposure*)	Extent to which PNs, GPs and older people actively engage in, interact with and are receptive to aspects of [G]OLD-protocol	Individual interviews PNs, GPs and older people
		Feedback sessions PNs
		[G]OLD care booklet for older people
*Dose received* (*satisfaction*)	Overall opinion of PNs, GPs, and older people about [G]OLD	Evaluation form training PNs
		Individual interviews
		Feedback sessions PNs
		[G]OLD care booklet for older people
*Reach* (*participation rate*)	Proportion of intended target population that participates in and completes the intervention:	Continuous registration by general practices and researchers
	(1) registration number and reasons for non-response and drop-out; (2) opinion PNs and GPs about reach	Individual interviews with PNs and GPs
*Context*	Environmental barriers and facilitators that influence implementation [G]OLD, continued involvement in [G]OLD, and/or study outcomes	Individual interviews with PNs and GPs
		Notes researchers and project leaders

Note: PN = practice nurse; GP = general practitioner.

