### Statistical analyses

We compute descriptive statistics to describe the characteristics of the target population and general practices and to investigate comparability of study groups at baseline. Relevant statistical tests (e.g., t-test, chi-square, analysis of variance, regression analysis) will be applied to analyse effects on primary and secondary outcome measures (level of significance is 0.05; two-tailed). Data will be analysed according to the intention-to-treat principle. In all analyses, there will be a correction for possible baseline differences between participants or general practices. In addition, we will perform sub-group analyses to investigate whether certain groups of older people benefit more from the [G]OLD-protocol than other groups. We will use the software package SPSS for Windows, version 17.0, for all statistical analyses.

Data gathered as part of the process evaluation will be analysed using descriptive techniques, such as calculating scores (e.g., number of drop-outs), narrative description of procedures, and identifying themes in the interviews.

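### Health care utilisation has no same-source baseline: three questionnaire items at T0, GP records and a booklet afterwards; the planned GP extraction could supply one at little cost

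*Protocol article*

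**What the plan says.** Table 2 operationalises health care utilisation as "Number of contacts with different health care providers (i.e., GP consultations, hospital admission" and gives it two rows. The first has three items at T0, which the table's footnote defines as a "postal questionnaire at the start of the study". The second has no item count and two follow-up sources. One is the GP Information System. The other is "continuous registration during study by older people in [G]OLD care booklet". No T1, T2 or T3 questionnaire items are listed for this outcome.

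Measures and data collection says of the GP source: "General practices register these outcomes continuously during the study period in the GP Information System and data are extracted for each patient after 18-months follow-up". It describes no extraction for a period before T0. Of the booklet it says "Older people receive this booklet at baseline" and that they are "requested to take it with them to each contact with professional health care providers for 18 months", so the booklet cannot supply a baseline either.

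Statistical analyses promises: "In all analyses, there will be a correction for possible baseline differences between participants or general practices". No change from baseline is specified for utilisation.

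**The concern.** In a randomised trial, a baseline covariate mainly gains precision. Here it has to carry part of the argument for comparability, because the two groups of practices were formed by other means:

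- Selection of general practices: intervention practices needed a practice nurse with time for older people, and one of the three regions was invited for the control group only.
- Target population: the number approached in intervention practices depended on nurse hours, while control practices approached everyone eligible. Non-responders were reminded by telephone in one group and by post in the other.

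Prior use of care and each practice's registration habits could therefore differ between the groups before the intervention starts. Both feed directly into a count of recorded contacts. If they are adjusted for poorly, a difference in recorded utilisation over 18 months may partly reflect what was already there.

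**Working it through.** The plan states no figure on this point, so the check compares the listed sources and then asks what each can adjust for.

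**Step 1. Sources by time point (Table 2; Measures and data collection).**

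| Outcome | T0 | Follow-up |
|---|---|---|
| RAND-36, GARS, attitude towards ageing | postal questionnaire | same questionnaire at T1, T2, T3 |
| Health care utilisation | three postal items | GP system and care booklet |

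Utilisation is the only outcome with a listed T0 measure whose source changes after baseline.

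**Step 2. What a proxy for prior use removes.** Let U be GP-recorded prior use and W the T0 self-report. Let r be their correlation within a group. With linear effects, random error in W that is the same in both groups, and no other covariates, adjusting for W leaves a share 1 − r² of the confounding by U. The document gives no r. Assuming 0.3 to 0.7:

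- r = 0.3: 1 − 0.09 = 0.91
- r = 0.5: 1 − 0.25 = 0.75
- r = 0.7: 1 − 0.49 = 0.51

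These are shares of an imbalance whose size is unknown and could be zero. They are not a bias in contacts. Other T0 covariates would lower them.

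**Step 3. What each baseline says about registration.** Suppose a practice registers a fraction c of its true contacts, and c is stable over time. Then:

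- log(recorded follow-up) = log c + log(true follow-up)
- log(recorded pre-T0) = log c + log(true pre-T0)

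The term log c appears in both lines. A same-source baseline therefore carries it and can remove it, fully if the coefficient on the log baseline count is 1 and partly if it is smaller. A self-report contains no c, so adjusting for it cannot remove differences in registration between practices. If c changes after T0, neither baseline corrects for the change.

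**Step 4. Is the better baseline within reach?** Study design and setting says practices selected participants from the GP Information System, so that system was in use before T0. An extraction per patient at 18 months is already planned. That contacts were registered in a comparable way before T0 is an assumption.

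**The case against.** The strongest reply is that the between-group comparison during follow-up is like for like: as written, both groups use the same two sources. No change score is planned, and a covariate need not come from the same instrument as the outcome. The correction is also not confined to the three items. It extends to differences between participants and practices, and T0 RAND-36, GARS and socio-demographic data are available. All of this stands. It makes the present adjustment weaker rather than invalid. It does not supply a baseline that carries registration completeness, and an analysis plan cannot use pre-T0 records that nobody extracts.

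The remedy also has a limit. Intervention nurses were trained, and completion of their instruments and care plans was checked monthly. Registration may therefore change after T0 in one group only, and a pre-T0 count would not correct for that.

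A reader might infer three stronger points that the document does not support:

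- **That the utilisation question cannot be answered at all.** This does not follow from an imperfect covariate when both groups share the follow-up sources.
- **That baseline and follow-up are in different units.** Table 2 gives one operationalisation for both rows, and the wording and recall period of the T0 items are not shown.
- **That the booklet inflates the intervention group's count with the intervention's own contacts.** The booklet goes to each professional contact, and Table 3 also lists it for dose received (exposure), defined as "Extent to which PNs, GPs and older people actively engage in, interact with and are receptive to aspects of [G]OLD-protocol". Inclusion is thus a fair inference, but no text says that nurse contacts count towards the outcome, and Table 2 names only GP consultations and hospital admission. If all contacts were summed, k protocol contacts on m usual ones would give a ratio of (m + k)/m with no true effect. Assuming k = 1 to 4 and m = 10 to 20, that is 21/20 = 1.05 to 14/10 = 1.40. Neither k nor m is in the document. Nurse results and follow-up also enter the electronic patient file, so the booklet is not the only source affected. Total care use including these contacts is a legitimate quantity. Which contacts to count, and which source is primary, is a choice of estimand or a detail that an article leaves to the fuller plan.

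**Conclusion.** The point holds as a cheap improvement to one secondary outcome. As described, prior utilisation can be adjusted for only through three self-reported items from a source not used at follow-up. In a design without randomisation this is a weaker adjustment than the planned data flow would allow, and it cannot address differences between practices in how fully contacts are registered.

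The size of any bias cannot be derived from the document. The range of 91% to 51% rests on an assumed correlation and on the simple error model in the working, and it applies to an imbalance of unknown size. The primary outcomes use the same questionnaire at all four time points and are not affected.

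**What to change.** In the GP-system extraction already planned at 18 months, also extract the same contact types for a fixed period before T0, for example 12 months, in both groups. Use that count as the baseline covariate for the GP-recorded utilisation outcome, and keep the three T0 items as a supplementary covariate.

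The cost is a wider date window in an existing extraction and a check that the consent covers records from before T0. No extra patient contact is needed. The report should say that this does not correct for registration habits that change after baseline.

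As a secondary suggestion only: [G]OLD home visits and nurse follow-up may appear in both the booklet and the electronic patient file, so report utilisation with and without these protocol contacts. Readers can then tell total care use from use of other care.

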### Process evaluation

A thorough process evaluation is conducted aiming to investigate to what extent the different components of the [G]OLD-protocol are implemented within general practices as planned (e.g., barriers and facilitators for implementation) and the feasibility of the protocol for both patients and caregivers. Ultimately, the results may provide information for further implementation of [G]OLD within general practices. Qualitative and quantitative process data are collected with either formative or summative purposes among GPs, practice nurses and older people according to the comprehensive and systematic approach proposed by Saunders and colleagues [41] (for details, see Table 3).

**Table 3 T3:** Data collection as part of the process evaluation

**Components**	**Operationalisation**	**Data collection Tools/****Procedures**
*Fidelity* (*quality*)	Extent to which the [G]OLD-protocol was implemented as planned	Evaluation form training PNs
		Individual interviews PNs, GPs and older people
		Feedback sessions PNs
		[G]OLD-instrument and care and treatment plan
*Dose delivered* (*completeness*)	Extent to which all aspects of [G]OLD-protocol are delivered to general practices and older people	Evaluation form training PNs
		Individual interviews PNs, GPs and older people
		Feedback sessions PNs
		[G]OLD-instrument and care and treatment plan
*Dose received* (*exposure*)	Extent to which PNs, GPs and older people actively engage in, interact with and are receptive to aspects of [G]OLD-protocol	Individual interviews PNs, GPs and older people
		Feedback sessions PNs
		[G]OLD care booklet for older people
*Dose received* (*satisfaction*)	Overall opinion of PNs, GPs, and older people about [G]OLD	Evaluation form training PNs
		Individual interviews
		Feedback sessions PNs
		[G]OLD care booklet for older people
*Reach* (*participation rate*)	Proportion of intended target population that participates in and completes the intervention:	Continuous registration by general practices and researchers
	(1) registration number and reasons for non-response and drop-out; (2) opinion PNs and GPs about reach	Individual interviews with PNs and GPs
*Context*	Environmental barriers and facilitators that influence implementation [G]OLD, continued involvement in [G]OLD, and/or study outcomes	Individual interviews with PNs and GPs
		Notes researchers and project leaders

Note: PN = practice nurse; GP = general practitioner.

The experience of practice nurses with the [G]OLD-protocol was assessed three times during one year (intervention period) by means of individual interviews. Results of these interviews were fed back to all practice nurses together during feedback sessions after six months and after one year (end of the intervention period). Additionally, GPs were individually interviewed at the end of the intervention period to assess their experiences with the implementation of [G]OLD within their general practice. One older person per general practice was selected for in-depth interviews about their experiences and satisfaction with all aspects of the [G]OLD-protocol, approximately one month after the [G]OLD-consultation took place. Furthermore, older people can register their satisfaction with contacts with professional care givers in the [G]OLD-care booklet. Finally, time required for the home visit, results of the tests performed and preliminary advise given to people during the home visit are registered by the practice nurse on the [G]OLD-instrument. Details about referral to care and/or well-being services are written down in the care and treatment plan. Members of the research team checked monthly during the intervention period to what extent the [G]OLD-instrument and the care and treatment plan were completely filled out. Practice nurses registered the patient’s follow-up within the chain of care in the electronic patient file from which relevant data can be extracted after 18-months follow-up.

### Sample size considerations

The sample size calculation is based on the primary outcome measure health-related quality of life (subscale ‘general health perception’) as measured by the RAND-36 [35,36]. We aim to demonstrate a clinically relevant difference between the mean change score of the intervention and control group of 5.0 on the transformed subscale. This implies a standardised effect size of 0.24 (given SD = 21.2). Based on this and applying a significance level (α) of 0.05 and a power of 0.90, the minimally required number of participants is 564 (n = 282 per study group) using an independent samples t-test (two-sided). However, calculations that take into account the interdependency of the measurements within a cluster (i.e., general practice) and correct for the cluster effect result in a required sample size of 1,200 older people (n = 600 per study group).

We expected a response rate of 50% on the information letter and consent form sent to eligible older people for participation and a drop-out rate of 30%. Accounting for drop-out, we planned to enrol 858 older people per study group to have a sufficient number of participants per group (600 older people) at the end of 18 months follow-up (see also Figure 1). Because of the expected response rate of 50%, we planned to approach at least 1,716 community-dwelling older people per study group for participation.

Since the amount of home visits that is performed depends on the PNs available time, we expected a variation in cluster sizes. This is compensated for by sampling 25% more clusters (i.e., general practices) [42].

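### The stated 282 per group gives about 80% power for the 5.0-point difference, not 90%; the cluster-corrected 600 probably inherits the error, but no intracluster correlation is given to confirm it

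*Protocol article*

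**What the plan says.** Everything needed is in the section Sample size considerations of the protocol article.

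- Endpoint: "The sample size calculation is based on the primary outcome measure health-related quality of life (subscale ‘general health perception".
- Target: a "difference between the mean change score of the intervention and control group of 5.0 on the transformed subscale".
- Spread: "This implies a standardised effect size of 0.24 (given SD = 21.2".
- Error rates: "applying a significance level (α) of 0.05 and a power of 0.90".
- Test: "using an independent samples t-test (two-sided".
- Size before clustering: "a power of 0.90, the minimally required number of participants is 564 (n = 282 per study group".
- Size after clustering: the cluster-adjusted calculations "result in a required sample size of 1,200 older people (n = 600 per study group".
- Enrolment: with 30% drop-out, "we planned to enrol 858 older people per study group". With a 50% response rate this leads to 1,716 approached per group.

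The section adds 25% more practices to allow for varying cluster size. It states no ICC, design effect or planned cluster size. The Abstract and the section Selection of general practices give 24 practices, 13 intervention and 11 control.

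**The concern.** All the inputs to a two-sample calculation are printed beside its result, so the claim can be checked without any outside figure, and it fails. The printed sample size belongs to 80% power, while the text claims 90%. At 282 per group the chance of missing a true 5.0-point difference is about 20%, twice the 10% claimed.

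This matters most if the result is null. The Background section calls the existing reviews of preventive home visits inconclusive. A null result here would be judged partly by the power the study claims, and a reader who trusts 0.90 would take it as stronger evidence against a 5.0-point benefit than the calculation supports.

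**Working it through.** **Inputs (Sample size considerations).** Difference 5.0; SD 21.2; two-sided alpha 0.05; power 0.90; equal groups; independent t-test. The standardised effect is 5.0/21.2 = 0.236, which agrees with the stated 0.24 after rounding.

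**Step 1: the stated figure.** Formula: n per group = 2 × (z for alpha + z for power)² × (SD/difference)², with (21.2/5.0)² = 17.98.

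- 90% power, two-sided: 2 × (1.960 + 1.282)² × 17.98 = 377.8, so 378 (exact t-test 379).
- 80% power, two-sided: 2 × (1.960 + 0.842)² × 17.98 = 282.2, which is 282 to the nearest whole number. Rounded up it is 283 (exact t-test 284).

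The stated 282 is therefore not reproduced at 90%, but is matched at 80%.

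**Step 2: power at 282 per group.** The expected test statistic is 5.0 / (21.2 × √(2/282)) = 2.80. Power is 80.0% (normal) or 79.8% (exact t).

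**Step 3: do other readings rescue 0.90?**

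| Reading | n per group, normal / t |
|---|---|
| Rounded effect 0.24, 90%, two-sided | 365 / 366 |
| 5.0/21.2, 90%, one-sided 0.05 | 308 / 309 |
| Rounded effect 0.24, 90%, one-sided 0.05 | 298 / 299 |

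None gives 282, and the article specifies a two-sided test. With the effect rounded to 0.24, power at 282 is 81.3% (normal) or 81.2% (t). For 282 to give 90%, the SD would have to be about 18.3 or the difference about 5.8; the article states neither. The use of change scores does not help, because the SD of 21.2 is applied directly to the difference in mean change.

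**Step 4: the later steps.** 600/0.70 = 857.1, so 858; 858/0.50 = 1,716. Both are correct given 600.

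**Step 5: power at 600 per group (conditional).** If 600 is 282 multiplied by a design effect, that effect is 600/282 = 2.13, and the effective size returns to 282.

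- Power for 5.0 points is then about 80% with a normal reference. It is 76.3% if the test uses a t distribution on 24 − 2 = 22 practice-level degrees of freedom.
- The difference detectable with 90% power is (1.960 + 1.282) × 21.2 × √(2/282) = 5.79 points with a normal reference, or about 6.1 on 22 degrees of freedom.

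**Step 6: range over the unstated ICC.** Assume 1,200/24 = 50 analysed per practice and a design effect of 1 + 49 × ICC. The implied 2.13 corresponds to ICC = 1.128/49 = 0.023. With 600 analysed per group:

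| Assumed ICC | Design effect | Power, normal | Power, 22 df |
|---|---|---|---|
| 0.01 | 1.49 | 92% | 89% |
| 0.02 | 1.98 | 83% | 79% |
| 0.023 | 2.13 | 80% | 76% |
| 0.03 | 2.47 | 74% | 70% |

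The table makes no separate adjustment for variable cluster size, which the article addresses with the 25% extra practices.

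**The case against.** The mismatch between 0.90 and 282 has no good defence. The objection concerns how far it reaches.

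A reader might infer that the whole study has 80% power, or 76% once the number of practices is allowed for. The article does not establish that. It says that the cluster-adjusted calculations lead to 600 but does not show 282 being multiplied by anything. Had 600 come from a separate cluster calculation correctly run at 90%, it would equal 379 × 1.58. That is an ICC of about 0.012 at 50 per practice, and power at 600 would be 90% (normal) or 87% (22 df). Nothing printed rules this out, although the text introduces 600 as the corrected version of the 282 calculation, so inflation of 282 remains the natural reading.

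The 76% figure needs a further assumption. It rests on a 22-df reference distribution that the article does not fix and may properly leave to the full analysis plan. It also ignores the planned correction for baseline differences, which could change precision. It belongs in the discussion as a conditional value and not as the headline.

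These objections stand, and they limit the claim about 600. They do not touch the error at 282. The 25% extra practices do not repair it either, because the article assigns them to variation in cluster size.

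**Conclusion.** The power statement for the unclustered calculation is wrong as written. On the article's own inputs 282 per group gives about 80% power, and 90% needs 378 to 379, so the stated number is about a quarter too low (282/379 = 0.74). This needs no assumption beyond what is printed.

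That 600, 858 and 1,716 carry the same shortfall is the likely reading but not a proven one. It rests on 600 being 282 inflated by 2.13, and the resulting 80% power at 600 also needs 2.13 to be the true design effect. Without the ICC and cluster size behind 600, the power of the study as planned cannot be recovered from the article.

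**What to change.** Keep the planned numbers and correct the text of Sample size considerations:

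1. State that 282 per group gives power 0.80 for 5.0 points with SD 21.2, two-sided alpha 0.05 and an independent t-test.
2. State the ICC and the cluster size used to reach 600 per group.
3. From these, restate the power at 600 analysed per group, or the difference detectable with 90% power. If the design effect is indeed 2.13, this is about 80% for 5.0 points, or 90% for about 5.8 points with a normal reference. If the planned test uses practice-level degrees of freedom, say so and give the power on that basis.
4. Use the restated figure when interpreting a null result.

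The change is to wording only. The stated power becomes less favourable; no extra participants are needed, and the conduct of the study is unaffected.
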